#### Instruments

2.2.1

The following screening instruments are being used for data collection:
The Center for Epidemiologic Studies Depression Scale (CES‐D)This scale was developed by the National Institute of Mental Health (NIMH) for epidemiological studies to detect depression in the general population.^25^ The CES‐D is a 20‐item self‐rating questionnaire that assesses symptoms of depression. The cut‐off value is 16 points, and a Japanese version of the CES‐D (CES‐D‐J) has been validated.^26^
The Edinburgh Postnatal Depression Scale (EPDS)The EPDS is a 10‐item self‐rating scale designed by British psychiatrist John Cox to screen for postpartum depression.^22^ The Japanese version of the EPDS was validated in 1996.^23^ Recently, the EPDS has also been shown to be a reliable and valid measure of maternal prenatal depression^27^ and is attracting attention as a rating scale for paternal perinatal depression.^8^ The diagnostic accuracy of the EPDS for postpartum depression in Japanese men has been reported to have a sensitivity of 81.8% and a specificity of 94.1% in the postpartum period, with a cutoff value of 8,^28^ but a similar study is lacking for the prenatal period.The Edinburgh Postnatal Depression Scale‐Partner (EPDS‐P)In regard to the original English‐language versions, the EPDS‐P was developed to assess postpartum depression in women from man’ perspective.^29^ In contrast, the EPDS‐P developed by Fisher et al.^24^ assesses paternal postpartum depression through maternal reporting. The diagnostic accuracy of the EPDS‐P has been reported to have a sensitivity of 89% and a specificity of 59% with a cutoff value of 4/5, but a Japanese version had yet to be developed. Therefore, with the help of [name], the English version of EPDS‐P for paternal depression was translated into Japanese, and back‐translated into English by three native speakers of Japanese and English and validated its Japanese version.The Mother‐to‐Infant Bonding Scale (MIBS)The MIBS is a self‐rating questionnaire that assesses a mother's feelings toward her infant.^30^ The MIBS includes 10 items that assess the mother–child bond.^31^ Each item is rated on a four‐point Likert‐type scale (0–3). The higher the MIBS score, the weaker the mother–child bond. The Japanese version of the MIBS has been previously validated and is commonly used in Japan to assess mother–child bonding.^31^

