### Outcome measures

2.3

The primary outcome will be accuracy of the EPDS‐P in determining paternal perinatal depression in Japanese men. Presence of paternal depression is determined based on the CES‐D, with a CES‐D total score of 16 or higher considered depression.

Then, ROC curves are drawn and AUCs are calculated to examine the discrimination accuracy of the two groups (depression or not) by EPDS‐P. Discriminatory value of ROC curves was interpreted as excellent (AUC 0.9–1), good (0.8–0.89), fair (0.7–0.79), poor (0.6–0.69), or fail/no discriminatory capacity (0.5–0.59).^32^ On the other hand, the point on the ROC curve where “sensitivity + specificity” is maximized is defined as the optimal cut‐off point. The sensitivity and specificity at the cutoff point are calculated, respectively.

The secondary outcome will be whether prenatal EPDS‐P can predict paternal postpartum depression using longitudinal data from pregnancy and the early postpartum period. Furthermore, we will calculate the correlation between the EPDS and CES‐D in men and analyze the performance of the EPDS in identifying paternal perinatal depression.

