### Sample size calculation

2.4

A meta‐analysis of reports based on self‐rating scales estimated the prevalence of paternal perinatal depression among Japanese men to be approximately 10%.^10^ Therefore, the sample size required to validate the accuracy of the EPDS‐P in the last trimester of pregnancy and within 3 months postpartum was estimated to be 554 at each time point, assuming a standard normal distribution, 95% confidence level, 0.025 margin of error (α/2), and 10% estimated value of the population proportion. Assuming a valid response rate of 90%, the target number of cases was set at 600 pairs for each time‐point. In Towada City, public health nurses have been making home visits to nearly all expectant and nursing mothers as part of the routine work of the maternal and child health care system since before this study began. An interview survey including the EPDS was conducted with women visited by these public health nurses, and cooperation was obtained in all cases. For this reason, we assumed that a high percentage of women would cooperate in the screening survey for paternal perinatal depression and therefore assumed the rate to be 90%. Given approximately 300 births per year and an extremely high rate (>95%) of home visits by public health nurses and midwives to expectant mothers in Towada City, the target number is expected to be achieved within a 30‐month survey period.

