### Data analysis plan

2.5

Upon completion of data collection, the database will be locked for statistical analysis. First, we will calculate the screening accuracy of the EPDS‐P, which in this study assesses depressive symptoms in men by women.

Men with a CES‐D score of 16 or higher are defined as the “depressed” group, and those with a CES‐D score of 15 or lower are defined as the “non‐depressed” group. ROC curves are drawn and AUCs are calculated to examine the discrimination accuracy of the two groups by EPDS‐P score. The discriminatory value of the ROC curves is interpreted as follows: excellent (AUC 0.90–1.00), good (0.80–0.89), fair (0.70–0.79), poor (0.60–0.69), or fail/no discriminatory capacity (0.5–0.59).^32^ The point on the ROC curve where sensitivity + specificity is maximized is defined as the optimal cut‐off point, and the sensitivity and specificity at the cut‐off point are calculated separately.

Next, we will determine the absolute value of Spearman's non‐parametric correlation coefficient between the EPDS‐P and CES‐D. We will also set men scoring 16 or higher on the CES‐D as the depressed group,^26^ and then perform a receiver operating characteristic (ROC) curves analysis to calculate optimal cut‐off values and sensitivity and specificity of the EPDS‐P. We also plan to examine the reliability of the EPDS‐P by calculating its Cronbach's alpha. Cronbach's alpha is the most widely used objective measure of reliability. Alpha is an important concept in the evaluation of assessments and questionnaires. Cronbach's alpha is a confidence coefficient that evaluates whether or not the items measure the same concept or object as a whole (internal consistency) when multiple questions are asked about a characteristic, and the sum of the responses is used as the characteristic scale.^33^ If the Cronbach's alpha coefficient for each item is above 0.6, it is considered to have good internal stability, reliability, and acceptable consistency for an exploratory study.^34^

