The cut‐off value of the EPDS‐P in detecting paternal depression will be calculated at two points: in late pregnancy and within 3 months postpartum. The statistical analysis did not include any participant's response having missing values or an inappropriate number of answers to a question item on a rating scale. Then, as a secondary analysis, we would like to stratify depressed and non‐depressed women, analyze the accuracy of the EPDS‐P in identifying paternal perinatal depression in each group, and examine the impact of women's mental status on the accuracy of the EPDS‐P.

In addition, we will examine the absolute value of Spearman's non‐parametric correlation coefficient between the CES‐D and EPDS in men and the accuracy of the EPDS in identifying depression in men. The depression group is defined as those with a CES‐D score of 16 or higher. Based on this, participants are divided into a depression group or a non‐depression group. We will also report the sensitivity and specificity of the cut‐off points for the EPDS in men at the pregnancy and postpartum. The global performance of the EPDS in men will be expressed as area under the ROC curve.

We will also analyze the characteristics of participants who first developed depression after childbirth.

As with maternal depression, paternal postpartum depression might develop during pregnancy, so we will calculate the proportion of cases of paternal postpartum depression that develop throughout the prenatal to postpartum period.

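### Any CES-D form with one unusable item is dropped, although the answered items often already settle whether the man is at 16 or above; the avoidable loss is modest

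*Protocol article*

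**What the plan says.** The Data analysis plan (section 2.5) states one rule for incomplete forms: it excludes every response "having missing values or an inappropriate number of answers to a question item on a rating scale". It gives no tolerance for a single blank, no prorating or imputation, and no sensitivity analysis.

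The reference standard is binary. Under Outcome measures (2.3), paternal depression is determined from the CES-D, "with a CES‐D total score of 16 or higher considered depression". Section 2.5 repeats the split for the EPDS-P, for the men's own EPDS and for the prenatal prediction of postpartum depression. Instruments (2.2.1) describes the CES-D as a "20‐item self‐rating questionnaire that assesses symptoms of depression". The score range of its items is not stated; a 0 to 3 range is given only for the MIBS.

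The Sample size calculation (2.4) uses a "10% estimated value of the population proportion" and then says: "Assuming a valid response rate of 90%, the target number of cases was set at 600 pairs" for each time point.

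**The concern.** The exclusion rule treats the CES-D as if its exact total were always needed. For the accuracy analyses it is not; only the side of the cut-off matters. A man whose answered items already total 16 or more is depressed by the plan's own definition, whatever the blank item would have added, and he is still removed. The same holds for a man whose answered items are so low that the blank cannot bring him to 16.

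It makes no difference whether the excluded response means the whole participant or only the affected questionnaire. Without a usable CES-D the man has no reference status and leaves every accuracy analysis.

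What is at stake is precision. The number of depressed men sets the precision of sensitivity and strongly limits that of the AUC, and at 10% prevalence there are few of them.

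**Working it through.** **The plan's own figure.** With p = 0.10, half-width d = 0.025 and 95% confidence, n = 1.96² × 0.10 × 0.90 / 0.025² = 553.17, rounded up to 554. This reproduces section 2.4. At 10% prevalence, 600 pairs hold about 60 depressed men.

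**Which forms are settled.** Let S be the sum of the answered items and k the number of unusable items. Assume each item scores 0 to 3.
- Depressed for certain if S ≥ 16. This needs only that item scores are not negative.
- Non-depressed for certain if S + 3k ≤ 15. For k = 1 this is S ≤ 12; for k = 2 it is S ≤ 9.
- Open otherwise: S = 13 to 15 for k = 1, and S = 10 to 15 for k = 2.

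**How often one blank leaves the class settled.** 400,000 men were simulated with 20 items scored 0 to 3, three spreads of severity, 10% at 16 or higher, and one item removed at random. The class stayed settled for 92.6%, 93.9% and 95.3% of all men, and for 85.7%, 87.8% and 90.3% of depressed men. Other simulations with different score distributions gave 91% to 96% of all men.

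**How many men the rule drops.** The item-missing rate q is not in the documents, so a range is shown. If blanks are independent across items and unrelated to depression, the share of CES-D forms with at least one blank is 1 − (1 − q)^20.

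| q per item | Share of forms | Of 600 men | Of 60 depressed | Exactly one blank, of 600 |
|---|---|---|---|---|
| 0.1% | 2.0% | 12 | 1 | 12 |
| 0.25% | 4.9% | 29 | 3 | 29 |
| 0.5% | 9.5% | 57 | 6 | 55 |
| 1% | 18.2% | 109 | 11 | 99 |

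At 0.5%, the single-blank forms alone would return about 54.5 × 0.926 = 50 to 54.5 × 0.953 = 52 men. Of about 5.5 depressed men with a single blank, 5.5 × 0.857 = 4.7 to 5.5 × 0.903 = 5.0 would return.

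**Effect on precision.** The protocol cites a sensitivity of 0.89 for the EPDS-P. The 95% half-width is 1.96 × √(0.89 × 0.11 / cases):
- 60 cases: 0.079
- 54 cases (6 lost): 0.083
- 49 cases (11 lost): 0.088

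**What a replacement rule must handle.**
- *Number of blanks.* With 3, 4 or 5 blanks a man can be certainly non-depressed only if S is at most 6, 3 or 0. With 6 blanks he never can be, because 6 × 3 = 18 exceeds 15. He could still be kept as a case with S ≥ 16. A certainty rule without a cap would therefore make inclusion depend on the outcome.
- *Rounding.* With one blank, the prorated total is S × 20/19, that is 13.7, 14.7 and 15.8 for S = 13, 14 and 15. Unrounded, every open form falls below 16, although about 19% to 34% of such men were truly depressed in simulation. Rounded to whole numbers the totals are 14, 15 and 16, so S = 15 is classed as depressed.

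**The case against.** Complete-form scoring is common, transparent and neutral with respect to outcome, and it contradicts nothing else in the protocol. The size of the loss rests on an assumed item-missing rate. If items are rarely missed, about one depressed man is lost. Even at 0.5% per item the half-width grows by only about 0.004. Blanks may also cluster, and then more incomplete forms have several blanks and fewer can be settled. All of this stands, and it keeps the point small.

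It could also be said that item-level scoring belongs in a fuller document. That does not answer the point, because the article itself states a rule and states it without exception.

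A reader might infer three stronger things, none of which the documents support:
- *That the loss falls mainly on depressed men because they skip more items.* Nothing in the protocol says so.
- *That the 90% valid response rate is out of reach because one blank in some 30 CES-D and EPDS-P items voids a couple.* Section 2.4 rests that rate on women's expected cooperation, not on item completeness, and the remedy here leaves EPDS-P exclusions as they are.
- *That the rule leaves the accuracy results unreliable.* The change in half-width does not bear that out.

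**Conclusion.** The point holds as a modest inefficiency. The plan discards men whose reference class is certain from the form they returned, and most of them can be kept without imputation. The upper bound (answered sum of 16 or more) needs only non-negative item scores. The lower bound assumes 0 to 3 scoring. For 600 men the loss runs from about 12 (1 depressed) at 0.1% blanks per item to about 109 (11 depressed) at 1%, with independent blanks unrelated to status. The half-width for a sensitivity of 0.89 moves from 0.079 to at most about 0.088 over that range. The change is worth making because it costs almost nothing, not because the loss threatens the study.

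**What to change.** In section 2.5, replace the whole-form exclusion for the CES-D, in the binary-status analyses only, with wording such as:

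*On CES-D forms with no more than two unusable items, a man is classed as depressed if his answered items total 16 or more, and as non-depressed if his answered items plus the maximum possible for the unusable items total 15 or less. Remaining forms with no more than two unusable items are classed from the prorated total, rounded to the nearest whole number (or by item-level multiple imputation). Forms with more than two unusable items are excluded whatever their sum.*

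Classing the open forms prevents selective loss of men near the cut-off. The cap prevents inclusion from depending on the outcome. State the CES-D item range in section 2.2.1. Report the complete-form analysis as a sensitivity analysis. The Spearman analyses need a total score, so they should use complete or prorated totals.

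The cost is a few sentences and a short scoring step, with no new data. The downside is that a few open forms near the cut-off rely on prorating or imputation. As analysis follows database lock, the rule can be fixed before any result is seen.

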We will examine whether EPDS‐P scores during pregnancy predict paternal postpartum depression. First, postpartum men will be divided into two groups: a depressed group (CES‐D total score of 16 or higher) and a non‐depressed group (CES‐D total score of 15 or lower). We will then draw an ROC curve using the EPDS‐P score during pregnancy and calculate the area under the ROC curve (AUC). The discriminatory value of the ROC curves will be interpreted as follows: excellent (AUC 0.90–1.00), good (0.80–0.89), fair (0.70–0.79), poor (0.60–0.69), or fail/no discriminatory capacity (0.50–0.59).^32^ If the AUC value is large, it is considered that the EPDS‐P score during pregnancy can discriminate paternal postpartum depression because EPDS‐P score during pregnancy can predict paternal postpartum depression. We will then determine the EPDS‐P optimal cutoff value during pregnancy that most accurately identifies paternal postpartum depression (the point on the ROC curve where sensitivity + specificity is maximized).

Furthermore, we will use a covariance structure analysis and binomial logistic regression analysis to test whether maternal EPDS score, MIBS score, and other maternal characteristics affect their EPDS‐P scores. All statistical analyses will be performed using IBM SPSS 28 and Amos 28 (IBM Japan, Tokyo, Japan).

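### The binomial logistic regression planned for EPDS-P scores needs a split outcome at an unnamed cut-off; a regression on the total score should answer that question instead

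*Protocol article*

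**What the plan says.** The question and its two methods stand in one sentence of section 2.5 (Data analysis plan), which names a covariance structure analysis and a "binomial logistic regression analysis to test whether maternal EPDS score, MIBS score, and other maternal characteristics affect their EPDS‐P scores". The same section gives the software: "All statistical analyses will be performed using IBM SPSS 28 and Amos 28". Neither method is named as the main one, and no cut-off is given for the logistic outcome.

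EPDS-P cut-offs appear elsewhere:

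- Section 2.5 sets the rule for a data-derived cut-off: "The point on the ROC curve where sensitivity + specificity is maximized is defined as the optimal cut‐off point". The EPDS-P cut-off for detecting paternal depression "will be calculated at two points: in late pregnancy and within 3 months postpartum".
- Section 2.5 derives a further cut-off on the pregnancy score for predicting postpartum depression in the father.
- The Introduction and section 2.2.1 (Instruments) cite a published cut-off, with "sensitivity of 89% and a specificity of 59% with a cutoff value of 4/5".

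The planned size (section 2.4, Sample size calculation) rests on the precision of one proportion. No power or effect size is stated for the analysis of maternal factors.

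**The concern.** The hypothesis concerns the score, but the logistic model can only address which side of a cut-off the score falls on. This has three consequences.

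1. The null hypothesis changes. The model asks whether a maternal factor alters the odds of exceeding the cut-off. Differences within either side are discarded.
2. The answer depends on a choice the plan leaves open. The ROC cut-offs are chosen to separate the fathers' CES-D groups, which has no bearing on how a mother's mood shifts her rating. If the cut-offs for the two time points were used and differed, the pregnancy and postpartum odds ratios would describe different outcomes.
3. Splitting a score loses information. For a weak influence, a finding of no maternal effect becomes more likely when an effect exists.

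The EPDS-P is the mother's rating of the father, so whether her own state moves that rating matters for an indirect screen. With two unranked methods, the logistic and score-based results could also disagree through dichotomisation alone.

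**Working it through.** **The plan's own figure.** Section 2.4 gives "95% confidence level, 0.025 margin of error (α/2), and 10% estimated value of the population proportion". Then n = 1.96² × 0.10 × 0.90 / 0.025² = 553.2, rounded up to 554, which matches. With 600 pairs and 90% valid responses, 600 × 0.90 = 540 are analysable. The check uses 540 to 554.

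**Share positive at 4/5.** From the published accuracy (section 2.2.1) and 10% prevalence (section 2.4): 0.10 × 0.89 + 0.90 × (1 − 0.59) = 0.089 + 0.369 = 45.8%. This is close to a median split.

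**Cost of splitting, normal score, two-sided 5%, one predictor (assumed).** If a share q is positive, the efficiency relative to the whole score is e = φ(z_q)² / (q(1 − q)). If the whole score has power P, the split score has power Φ((1.96 + z_P)√e − 1.96). Example for q = 0.10 and P = 0.80: e = 0.1755² / 0.09 = 0.342; (1.96 + 0.842) × 0.585 − 1.96 = −0.32; power 37.4%.

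| Share positive | e | Power if whole score has 80% | Loss (points) | Loss if whole score has 90% (points) |
|---|---|---|---|---|
| 50% | 0.637 | 60.8% | 19.2 | 16.6 |
| 45.8% (4/5) | 0.634 | 60.7% | 19.3 | 16.7 |
| 40% | 0.622 | 59.8% | 20.2 | 17.5 |
| 30% | 0.576 | 56.6% | 23.4 | 20.9 |
| 20% | 0.490 | 50.0% | 30.0 | 27.9 |
| 10% | 0.342 | 37.4% | 42.6 | 42.5 |

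**Which correlation this corresponds to.** By Fisher's z with n = 540, power = Φ(atanh(r)√537 − 1.96), with r√e in place of r for the split score.

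- r = 0.12: 79.8% on the whole score, about 80%.
- r = 0.15: 93.9%, falling to 79.6% at a median split and 53.1% at 10% positive.
- r = 0.20: 99.7%, falling to 96.2% and 77.7%.
- r = 0.25: almost 100%. The loss is 0.3 to 0.6 points with 30% to 50% positive, 1.6 at 20% and 7.3 at 10%.
- r = 0.30: no visible loss at 30% to 50% positive, 1.6 points at 10%.

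**Simulations, n = 540.**

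- *Normal score, r = 0.12, 1,000 runs.* Linear regression 80%; logistic regression 57% at a median or 4/5-type split, 49% at 20% positive and 37% at 10%.
- *Right-skewed count score, mean 4.8, 1,000 runs.* At a similar effect, linear 83% against logistic 57% to 64% across four cut-offs, a loss of 18 to 26 points. At the next larger effect, 95% against 74% to 82%, a loss of 14 to 21 points.
- *Skewed score, mean about 4, two maternal predictors correlated 0.4, linear model on log(1 + score), 1,500 runs.* Type I error was about 5% for both models. At a cut-off of 4/5 (33% positive in that model), power was 0.70–0.72 against 0.50 at r = 0.12, and 0.91–0.92 against 0.73 at r = 0.16: losses of 20–22 and 18–19 points.

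The simulations agree with the formula on direction and order of size. The skewed results show that the loss at a given share positive also depends on the shape of the score.

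**The case against.** The strongest reply is that the same sentence already plans a covariance structure analysis, with Amos specified in the software line, and that this method can keep the whole score. This stands. A reader might infer that maternal influence will be judged only by a weak test on a split score; the protocol does not support that. What remains is that one of two unranked methods does not fit its stated outcome.

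A reader might also take a loss of 20 points or more as a general result. The documents do not support that either. They give no effect size and no cut-off for this analysis, the 4/5 split their own figures imply costs about 19 points at 80% whole-score power and about 17 at 90%, and the loss nearly vanishes for moderate correlations unless the cut-off is extreme.

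The cut-off may be coded in a fuller document. That is fair, so its absence alone is not the point. Naming a binary model for a score outcome is a stated choice, and fixing the cut-off later would not make it a test of the score. Non-comparability between time points is likewise conditional: it arises only if different cut-offs are used.

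Screen-positive status is a legitimate operational question for a screening tool, but the sentence does not pose it. Section 2.5 also plans to compare EPDS-P accuracy between depressed and non-depressed women, which addresses the threat to the screen more directly and limits the harm.

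Finally, the Introduction reports that maternal and paternal depression risks are correlated. An association between maternal EPDS and EPDS-P may therefore partly reflect true paternal depression. Regression on the score does not remove that ambiguity.

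**Conclusion.** The point holds as a minor one. The binomial logistic model tests the odds of crossing a cut-off that is not named for this analysis, while the stated question is about EPDS-P scores.

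Under a normal score, one predictor, two-sided 5% and 540 to 554 pairs, the power loss for a weak association (r about 0.12) is about 19 points near the middle of the distribution, 23 at 30% positive, 30 at 20% and 43 at 10%. At r = 0.25 it is under 1 point with 30% to 50% positive. Effect size, cut-off and score shape are all assumptions, so the size should be read as a range.

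The analysis is additional: it is neither the primary nor a listed secondary outcome in section 2.3 (Outcome measures). A second method in the plan can use the whole score.

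**What to change.** In section 2.5, replace the binomial logistic regression for this question with a regression on the EPDS-P total score at each time point, using the same maternal predictors at both. Either a proportional-odds ordinal model or a linear model on log(1 + score) would do. State that this analysis, alongside the covariance structure model, answers whether maternal factors affect EPDS-P scores.

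If a binary model is kept, describe it as a supplementary analysis of screen-positive status, with one cut-off fixed in advance and used at both time points.

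The cost is a short wording change before database lock. SPSS 28 fits these models and no new data are needed. The small downside is that the main coefficients are no longer odds ratios for screen-positive status.
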